### Aim

The aim of the trial is to compare the effects of an Internet-based neck-specific exercise programme (NSEIT) with the same exercises (NSE) performed at a physiotherapy clinic in regards to self-reported and clinical measures, as well as cost-effectiveness. Further objectives are to identify factors associated with the outcome following exercise regarding pain and disability.

Hypothesis: Internet-based neck-specific exercises with four visits to the physiotherapist will be non-inferior to neck-specific exercises at a physiotherapy clinic twice a week for 12 weeks (i.e., treatment NSEIT is not inferior to NSE) at 3- and 15-month follow-ups, and NSEIT yields lower economic costs for society than NSE.

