### Variables and measurements

All questionnaires will be answered electronically through a website. Participants will receive a disposable code e-mailed by a project team member to log in to the system (not the first survey before study inclusion). The electronic questionnaire cannot be submitted if the core outcomes are not answered. If a participant does not answer the questionnaire after two reminders (1.5 weeks after it is due and after another 1.5 weeks), a project team member not involved in the randomization procedure will phone the patient to collect the core outcomes of the NDI and pain variables. The Web-based questionnaire has been tested by both the project group and people with chronic neck pain (including WAD) and adjusted thereafter. Clinical measurements will be performed by test leaders in primary care settings in the different counties involved in the study.

Background data that will be collected include age, sex, family status, symptom duration, former healthcare, education, occupational classification (“Standard for Swedish work classification” SSY code [72]), post-traumatic stress reactions using the Post-traumatic Stress Disorder checklist (PCL-S) [73, 74], and the expectation of future treatment.

The primary outcome measure that will be collected is neck-specific function as measured by the NDI [71] (for example of the data collection form, please see http://www.aaos.org/uploadedFiles/NDI.pdf).

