Secondary outcome measures that will be collected include neck-related function as measured by the Whiplash Disability Questionnaire [75–77] and patient-specific functional scale [78]; pain intensity in the neck, head, and arm (0–100 mm VAS) [70]; distribution of pain (Pain Sketch app) [79]; frequency of pain as measured by a 5-grade scale and use of pain medications; dizziness/balance according to the Dizziness Handicap Inventory (DHI) [80] and VAS [70]; headache according to a VAS [70] and the Headache Impact Test (HIT-6) [81]; cognitive ability according to the Cognitive Failures Questionnaire (CFQ) [82]; catastrophizing according to the Pain Catastrophizing Scale [83]; confidence in ability (Self-Efficacy Scale) [84]; operating fear according to the Fear Avoidance Beliefs Questionnaire (FABQ) [85, 86]; depression and anxiety measured with the Hospital Anxiety and Depression Scale (HAD) [87]; self-rated work ability measured by the Work Ability Index (WAI) [88–90]; sick days recorded (number of days/part of days, and dates of periods of sick days according to the Social Insurance Agency MIDAS register); income according to the Swedish tax office; health-related quality of life (EuroQuol) [91]; Global Rating of Change Scale [92]; requirements-effort support in the workplace according to the Effort Reward Imbalance [93]; ergonomics and how work is perceived; sickness presence (Stanford presenteeism scale) [94, 95]; self-assessment of sick-leave and data from the social security office; expectations and satisfaction with healthcare fulfilled by Cherkin Symptoms Satisfaction [96] and Patient Enablement Instrument [97] and questions of how they perceived study participation; level of physical activity measured with two questions about daily activities and sports [98, 99]; and adherence to treatment according to an exercise diary. Self-assessed care consumption and data obtained from the county council’s healthcare database or similar will be used in the cost-effectiveness analysis, and self-assessed consumption of analgesic drugs and data from the drug registry will also be collected. Two reminders will be send to participants who do not answer the questionnaires.

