Analyses will be performed in collaboration with a statistician using parametric or non-parametric statistics depending on the type of data and whether the analysis is between groups or over time. Analyses will be performed primarily on an intention-to-treat basis (as individuals being randomized into the two groups) and secondarily on a per protocol basis (counted on individuals who fulfilled the programme for at least 50%). Imputation methods may be used when deemed to have additional value. Subgroup analyses of age, gender, WAD grade, headache, and dizziness may possibly be performed. Database monitoring will be performed by the project leaders and statisticians involved after study completion, independent of sponsors and competing interests. The project leaders and collaborating statisticians and researchers will have access to the final trial dataset (after the project leaders’ allowances).

Background data will be evaluated by descriptive statistics and differences in baseline data determined using t-test (mean and standard deviation) or non-parametric test where appropriate. A linear mixed model or general linear mixed model (GLMM) may be used depending on the data. NDI will be evaluated as a dependent variable with independent fixed factors time (baseline, 3 months, and 15 months after start of intervention) and group (A and B). If the non-inferiority of B to A is concluded based on the 95% CI, a test of the superiority of B to A will be performed as suggested by Lessafre [110]. Cost-effectiveness will be calculated from both a societal and healthcare perspective using incremental cost-effectiveness ratios (ICERs) based on the EQ-5D for QALY calculations. The variation in response to intervention (heterogeneity of treatment effect) will be evaluated using regression analysis.

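### The telephone follow-up of non-responders omits EQ-5D, so participants reached that way have no observed utility for the QALY analysis at that visit

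*Protocol article*

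**What the plan says.** All references are to the Protocol article.

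- **Variables and measurements, web form.** Questionnaires are answered electronically, with one stated lock: "The electronic questionnaire cannot be submitted if the core outcomes are not answered".
- **Variables and measurements, telephone call.** The trigger is stated as "If a participant does not answer the questionnaire after two reminders (1.5 weeks after it is due and after another 1.5 weeks", about three weeks after the due date. The plan is then that "a project team member not involved in the randomization procedure will phone the patient to collect the core outcomes of the NDI and pain variables".
- **Variables and measurements, outcomes.** The NDI is primary. The EuroQol instrument appears once, in a long list of secondary outcomes.
- **Statistical analysis.** Cost-effectiveness is to be calculated "using incremental cost-effectiveness ratios (ICERs) based on the EQ-5D for QALY calculations", from a societal and a healthcare perspective. Imputation is permitted but optional, with no method named.
- **Aim.** Cost-effectiveness stands beside the self-reported and clinical measures. The economic part of the hypothesis is that "NSEIT yields lower economic costs for society than NSE".
- **Recruitment and randomization.** Nobody enters the trial without a full set of baseline measurements.

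**The concern.** The telephone call is the plan's last defence against a missing questionnaire, and its content is fixed. It secures the primary outcome and pain but not the only instrument from which QALYs are to be computed. Someone who ignores both reminders and then answers the telephone contributes an NDI for that visit and no utility.

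An analysis plan can say how to handle such gaps, but it cannot recover answers that were never asked for. People who need a telephone call may well differ from prompt responders. The frequency of such calls might also differ between arms with 4 and 24 clinic visits. Both are plausible, but the article shows neither. At stake are the precision of the utility side of the cost-effectiveness analysis and how far it depends on imputation.

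**Working it through.** **The plan's own figure.** The only sample-size figure is 47 per group for the NDI, with margin 7, SD 13.4, one-sided 5% and 80% power.

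n = 2 × (1.645 + 0.842)² × 13.4² / 7² ≈ 45.3, so 46 by the normal approximation. The t-based calculation gives 47. The figure reproduces, and the present point does not depend on it. The article gives no figure for EQ-5D, QALYs or telephone contacts.

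**Weight of the follow-up values.** The visits are at 0, 3 and 15 months. If utility is joined by straight lines (my assumption; the article does not give the QALY formula), the weights in years are:

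- baseline: 0.25/2 = 0.125
- 3 months: 0.25/2 + 1/2 = 0.625
- 15 months: 1/2 = 0.5

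The total is 1.25 years. The two follow-ups carry 1.125/1.25 = 90% of it, so the secured baseline value does not by itself protect the QALY.

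**How many participants are affected.** Assumptions, none of them from the article:

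- r = share not answering after two reminders, the same at both follow-ups, 10% to 25%
- telephone reach = two thirds
- no other loss to follow-up
- every submitted web form contains EQ-5D

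Two patterns of non-response bracket the answer.

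*Same people both times* (and the same two thirds reached both times): complete EQ-5D = 140 × (1 − r) without EQ-5D in the call, and 140 × (1 − r/3) with it.

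*Independent at the two visits:* 140 × (1 − r)² without, and 140 × (1 − r/3)² with.

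| r | Pattern | Without | With | Gain |
|---|---|---|---|---|
| 10% | same people | 126 | 135 | 9 |
| 10% | independent | 113 | 131 | about 17 |
| 15% | same people | 119 | 133 | 14 |
| 15% | independent | 101 | 126 | 25 |
| 25% | same people | 105 | 128 | 23 |
| 25% | independent | 79 | 118 | 39 |

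Example, r = 25%, independent: 140 × 0.75² = 78.75, and 140 × 0.9167² = 117.6.

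**Effect on precision in a complete-case analysis.** The ratio of standard errors, without to with, is the square root of the inverse ratio of the numbers. At 10% it is √(135.3/126) = 1.04 to √(130.8/113.4) = 1.07. At 25% it is √(128.3/105) = 1.11 to √(117.6/78.75) = 1.22.

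**The case against.** A reader might infer that QALYs cannot be derived at all for these participants, and that the cost-effectiveness answer therefore rests on a smaller, selected sample. The document does not support that.

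- **Imputation is open.** The Statistical analysis section makes intention-to-treat primary and allows imputation. A participant who misses one follow-up still has baseline EQ-5D and usually the other follow-up, and the call itself supplies NDI and pain as predictors. A selected sample follows only from a complete-case economic analysis, which the article nowhere specifies.
- **Numbers are unknown.** Reminders come first and apply to the whole questionnaire. Nothing prevents a participant who has been telephoned from still submitting the web form. The number left without EQ-5D could be close to zero.
- **The lock may already cover EQ-5D.** The compulsory fields are described only as core outcomes. That these are just the NDI and pain is inferred from the use of the same term for the call.
- **Costs are less exposed.** The stated economic hypothesis concerns costs. These draw partly on sick-leave, income, healthcare and drug registers, and physiotherapists record care contacts.
- **A short call is defensible.** Limiting it to the primary outcome and pain protects the primary endpoint, and EQ-5D is secondary.

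The first four limit the consequence, and I accept them. The last explains the choice but does not remove the gap. QALYs serve a named aim, registers hold no utilities, and modelling EQ-5D from the NDI is weaker than asking for it in a call that is being made anyway.

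**Conclusion.** The point holds in a limited form. As written, the telephone call yields no observed EQ-5D at that follow-up, and the QALYs of those participants must be dropped or imputed under a provision that the article leaves optional. This is an avoidable weakness in a named aim. It is neither an error in the primary analysis nor a bar to a cost-effectiveness analysis.

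Under the assumptions above, EQ-5D in the call would complete the series for about 9 to 17 more participants of 140 at 10% non-response and 23 to 39 more at 25%. The lower end of each range applies if the same people fail to respond both times. These sizes rest entirely on assumed non-response and telephone-reach rates. Selection bias and differential loss by arm remain possibilities only.

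**What to change.** In Variables and measurements:

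1. Add EQ-5D to the items asked in the telephone call, beside the NDI and the pain variables.
2. Make EQ-5D compulsory for submission of the web form, if it is not already.
3. Flag telephone-collected values in the database, so that a sensitivity analysis can allow for the mode of collection.

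This needs a few more questions in a call already planned and a setting in the electronic form. It needs no added visits or staff. The downsides are a slightly longer call and a possible small difference between spoken and web answers. The change helps only follow-ups still to come, so it should be made early. For values already missed, the analysis plan would have to state how EQ-5D is imputed, and it may already do so.

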### Ethical considerations

The study was approved by the regional ethical review board in Linköping, Sweden. A previous clinical study relating to three different exercise interventions for long-term problems after whiplash injury [10, 11, 18–20] demonstrated good efficacy of neck-specific exercise performed in a primary healthcare setting. Current treatment is according to the best scientific evidence, and exercises used in the present study have been used in daily clinical practice for decades in the rehabilitation of various forms of neck pain. All of the physical tests are well-established and used both clinically and in previous research studies, are non-invasive, and do not cause danger or harm to the individual except for some risk of muscle soreness. Participants are included after a thorough clinical examination and provide signed informed consent. The exercises are adjusted individually. Participants are insured by the Swedish Legal, Financial, and Administrative Services Agency (Kammarkollegiet).

Login is required to fill in Internet-based surveys and to gain access to the Internet-based exercise programme. If the effect of the Internet-based exercise programme is good, the researchers’ intention is that it be used in clinical practice. People with long-term problems often have little access to assessments and treatments, as more acute conditions are often prioritized in the healthcare system. Both groups in the present study get active care that is expected to increase work ability. The benefit is deemed to be great, and there are no commercial interests.

The results will be presented at the group level, and no connection to the individual person can be made. All data are anonymous and subject to the official health secrets act.

### Statistical analysis

Sample size and power regarding group differences were calculated by a statistician (non-inferiority trial, an assumption that treatment B is not inferior to A) in the software PASS (version 13.0.8) based on the primary outcome NDI [71]. To detect a clinically relevant improvement of 7% in the NDI, 47 participants are needed in each group for 80% power. For non-inferiority tests, the significance level was set to 5% (*p* > 0.05), which corresponds to the one-sided confidence interval (95% CI). To be improved, both groups need a 7% increase in NDI (mean or median value depending on data) [71, 108, 109]. A non-inferiority border of less than 7% was chosen for mean NDI scores because it is on the border of what would be considered a clinically important effect [71, 108]. In addition, for secondary outcomes, the mean/median score will be on the border of what would be considered a clinically important effect for each measurement. The 95% CI will be examined and, if the upper limit of the interval is less than the chosen border value, non-inferiority of NSEIT to NSE will be concluded. For background data, and if appropriate after the non-inferiority test, a two-sided superiority test will be performed with a significance level of 5%. These values are based on the standard deviation (SD 13.4) of the NDI in a previous study of neck-specific exercises in individuals with chronic WAD grade 2 and 3 [18, 19]. To ensure that enough people are in each group after drop-outs, for prediction analyses, and the opportunity for subgroup analyses, 70 participants will be included in each group.

Analyses will be performed in collaboration with a statistician using parametric or non-parametric statistics depending on the type of data and whether the analysis is between groups or over time. Analyses will be performed primarily on an intention-to-treat basis (as individuals being randomized into the two groups) and secondarily on a per protocol basis (counted on individuals who fulfilled the programme for at least 50%). Imputation methods may be used when deemed to have additional value. Subgroup analyses of age, gender, WAD grade, headache, and dizziness may possibly be performed. Database monitoring will be performed by the project leaders and statisticians involved after study completion, independent of sponsors and competing interests. The project leaders and collaborating statisticians and researchers will have access to the final trial dataset (after the project leaders’ allowances).

Background data will be evaluated by descriptive statistics and differences in baseline data determined using t-test (mean and standard deviation) or non-parametric test where appropriate. A linear mixed model or general linear mixed model (GLMM) may be used depending on the data. NDI will be evaluated as a dependent variable with independent fixed factors time (baseline, 3 months, and 15 months after start of intervention) and group (A and B). If the non-inferiority of B to A is concluded based on the 95% CI, a test of the superiority of B to A will be performed as suggested by Lessafre [110]. Cost-effectiveness will be calculated from both a societal and healthcare perspective using incremental cost-effectiveness ratios (ICERs) based on the EQ-5D for QALY calculations. The variation in response to intervention (heterogeneity of treatment effect) will be evaluated using regression analysis.

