## Methods/design

### Design

This is an experimental, longitudinal, prospective, multicentre, randomized controlled trial (RCT) with two parallel treatment arms conducted according to a detailed protocol decided on before recruitment started (ClinicalTrials.gov Protocol ID: NCT03022812). Physiotherapist-led neck-specific exercise previously shown to be effective for the current population [18, 19] constitutes the control treatment for the new Internet-based neck-specific exercise treatment. A total of 140 people (70 in each group) are expected to be included, mainly by self-selection after advertisements. Independent physiotherapists in primary care will distribute the treatment. Due to the nature of the study, neither participants nor treating therapists can be blinded. To be un-biased to data the project manager will not be involved in the data collection. The physical measurements will instead be performed by independent test-leaders/specially trained, skilled, physiotherapists blinded to randomization. Data collection in the form of questionnaires and tests of physical neck-related function occurs at baseline (before randomization) and after 3 (end of physiotherapy rehabilitation) months and 15 months (1 year post-intervention) (Table 1). The study has been approved by the regional ethics committee in Linköping, Sweden (Dnr 2016/135–31; 2016/526–32; 2017/45–32). Recruitment started April 6, 2017 (Fig. 1) and is planned to continue until the 140 participants have been recruited.

**Table 1 Tab1:** Schedule of enrolment, interventions, and assessments

	STUDY PERIOD					
	Enrolment	Allocation	Post-allocation			Close-out
			*t* _*1*_	*t* _*2*_	*t* _*3*_	*t* _*x*_
TIMEPOINT^c^	*0*	0				
ENROLMENT						
Eligibility screen	X					
Informed consent	X					
Allocation		X				
INTERVENTIONS^a^						
NSE			X	X	X	
NSEIT			X	X	X	
ASSESSMENTS^b^						
Demographic data	X		X			
Self-reported outcomes (questionnaires)			X	X	X	X
Clinical outcome			X	X	X	X

^a^NSE = 12 weeks of neck-specific exercise at physiotherapy clinic, NSEIT = 12 weeks of neck-specific exercise with 4 appointments at physiotherapy clinic + Internet support

^b^Questionnaires on various aspects of disability, pain, psychosocial factors, etc., including the main outcome the Neck Disability Index. Clinical outcomes including neck muscle endurance, range of motion, neurological tests, etc.

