### Study population

Individuals with a whiplash injury from a traffic accident with a four-wheeled motor vehicle at least 6 months ago but less than 5 years ago will be included after written and oral informed consent if they have chronic neck problems corresponding to WAD grades 2–3 [7] verified by clinical examination and have not participated in a neck-specific exercise programme in a previous research study [18, 19]. Additional inclusion criteria are: average estimated pain in the last week at least 20 mm on the visual analogue scale (VAS) [70], neck disability of more than 20% on the Neck Disability Index (NDI) [71], working age (18–63 years), daily access to a computer/tablet/smart phone and Internet, time to follow the treatment programme, and neck symptoms within the first week after the injury (i.e., neck pain, neck stiffness, or cervical radiculopathy).

Individuals with any of the following signs of head injury at the time of whiplash injury will be excluded: loss of consciousness, amnesia before or after the injury, altered mental status (e.g., confusion, disorientation), focal neurological changes (changes in smell and taste). Additional exclusion criteria are previous fractures or dislocation of the cervical column; known or suspected serious physical pathology included myelopathy, spinal tumours, spinal infection, or ongoing malignancy; previous severe neck problems that resulted in sick leave for more than a month in the year before the current whiplash injury; surgery in the cervical column; generalized or more dominant pain elsewhere in the body; other illness/injury that may prevent full participation in the study and/or in which neck exercises are contraindicated; inability to understand and write in Swedish; diagnosed severe mental illness, such as psychosis, schizophrenia, personality disorders; or current alcohol and drug abuse.

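### The improvement criterion for the primary outcome has the wrong sign: it asks for a rise in a disability score

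*Protocol article*

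**What the plan says.** Four statements in the protocol article bear on the direction of the NDI.

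- **Study population.** Entry requires "neck disability of more than 20% on the Neck Disability Index (NDI"), so the score is read as an amount of disability.
- **Design, footnote b to Table 1.** The NDI is listed under "Questionnaires on various aspects of disability, pain, psychosocial factors, etc., including the main outcome the Neck Disability Index".
- **Statistical analysis, improvement criterion.** "To be improved, both groups need a 7% increase in NDI (mean or median value depending on data").
- **Statistical analysis, non-inferiority rule.** The margin is given as "A non-inferiority border of less than 7% was chosen for mean NDI scores", and the conclusion is drawn "if the upper limit of the interval is less than the chosen border value, non-inferiority of NSEIT to NSE will be concluded".

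The sample-size sentence in the same section refers to change without a sign: "To detect a clinically relevant improvement of 7% in the NDI, 47 participants are needed in each group for 80% power". Variables and measurements describes the primary outcome as "neck-specific function as measured by the NDI", which gives no scoring direction.

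**The concern.** A plan that sets a threshold for improvement on the primary outcome has to state the direction of change correctly. Here the only explicit statement about the direction of NDI change calls a rise an improvement, on a scale where a rise means more disability. Applied literally, the criterion would report a group that got worse as improved and a group that got better as not improved.

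The description of the NDI as a measure of function makes the slip easier to miss, because on a function scale an increase would naturally be good. The sentence also sits beside a non-inferiority rule that makes sense only if higher is worse, so one paragraph implies two scale directions for one endpoint. What is at stake is the within-group statement of whether each arm improved.

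**Working it through.** **1. Scale direction.** The entry criterion sets a floor of 20% disability on the NDI, and the footnote to Table 1 places the NDI among the disability questionnaires. Both mean that higher is worse. Nothing in the article reverses the scale.

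**2. The criterion applied literally.** Take an illustrative baseline group mean of 40 (an assumed value; any baseline gives the same result) and a change of 7 points:

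| Change in group mean | Meaning on a disability scale | Literal criterion |
|---|---|---|
| 40 to 47 (+7) | worse | improved |
| 40 to 33 (−7) | better | not improved |

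The labels are exactly reversed.

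**3. The plan's sample size.** Inputs from Statistical analysis: margin 7, SD 13.4, one-sided 5%, power 80%. Assumed: true difference 0 and 1:1 allocation.

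n per group = 2 × (1.645 + 0.842)² × 13.4² / 7² = 2 × 6.185 × 179.56 / 49 ≈ 45.3, rounded up to 46.

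The exact t calculation gives power 0.79997 at 46 and 0.8075 at 47, so 47 per group, as stated. The formula uses only the size of the margin and the SD. Replacing *increase* with *decrease* leaves it at 47. It also treats 7 as points in the same units as the SD, which supports reading the 7% as percentage points of the score.

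**4. The non-inferiority rule on the raw NDI.** Let the difference be NSEIT minus NSE, so that positive means NSEIT is worse. The standard error is 13.4 × √(2/n):

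- n = 47: 2.76
- n = 70: 2.27

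The probability that the one-sided 95% upper limit is below 7 is Φ((7 − true difference)/SE − 1.645):

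- True difference +7 (NSEIT worse by the margin): Φ(−1.645) = 0.05 at either n, the intended error rate.
- True difference 0: Φ(7/2.76 − 1.645) ≈ 0.81 at 47 per group; Φ(7/2.27 − 1.645) ≈ 0.93 at 70 per group.

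The rule therefore works as intended on a scale where higher is worse. That is the scale the entry criterion uses, and the opposite of the one the improvement sentence implies.

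**The case against.** The intended meaning can be recovered. The sentence opens by speaking of being improved, and two sentences earlier the section refers to an improvement of 7%. The entry criterion makes the direction of the scale plain. An analyst who knows the NDI would probably read the word as a slip for *improvement* or *reduction*. This stands, and it is why the point is minor. It does not make the sentence right: a stated criterion should not depend on the reader inverting it.

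Three stronger readings are tempting, and the article does not support them.

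- **That the sentence contradicts the non-inferiority rule, or makes it wrong.** One concerns change within each group and the other a difference between groups. They imply different scale directions but are not two versions of one rule. The non-inferiority rule is sound on the raw NDI.
- **That the trial could pass a clearly worse NSEIT.** This would require recoding the NDI into improvement scores while keeping the upper-limit rule. The article describes no recoding: the margin is set for mean NDI scores, and the NDI itself is the dependent variable in the model.
- **That the criterion is the safeguard against claiming non-inferiority between two ineffective arms.** No text makes within-group improvement a condition for concluding non-inferiority or for going on to test superiority.

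The order of subtraction is not stated, but a condensed article may leave that to the full protocol or analysis plan, so its absence is not a fault here.

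**Conclusion.** The point holds as a minor but real correction. The within-group improvement criterion for the primary outcome is reversed as written, and the reversal is complete: any change that meets the literal threshold is a worsening of disability.

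The error does not reach the primary comparison. The 47 per group, the margin of 7, the one-sided 5% level, the power (about 0.93 at 70 per group with no drop-out) and the non-inferiority rule are all unaffected.

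The conclusion about direction rests only on the article's own entry criterion and its description of the NDI. Reading the rule as sound assumes that the difference is NSEIT minus NSE on the raw score, which is the usual order and fits the rule's wording but is not stated.

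**What to change.** In Statistical analysis, replace the word *increase* with *decrease*, so that the criterion reads in substance: a group is improved if its mean (or median) NDI falls by at least 7 percentage points from baseline.

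Optionally, add one clause saying that the non-inferiority interval is for NSEIT minus NSE in NDI score, with positive values meaning NSEIT is worse. This clarifies the existing rule without changing it.

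The cost is a one-word correction plus, if wanted, one clause. No recalculation, redesign or change to data collection is needed.

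### As listed, the NDI model terms pool the pre-randomization visit and do not give the 3- and 15-month comparisons; testing its group coefficient would favour non-inferiority

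*Protocol article*

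**What the plan says.** The Aim section states the hypothesis by visit: "treatment NSEIT is not inferior to NSE) at 3- and 15-month follow-ups". The Design section says that data collection "occurs at baseline (before randomization) and after 3 (end of physiotherapy rehabilitation) months and 15 months", so the first NDI value precedes allocation.

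The Statistical analysis section says of modelling: "A linear mixed model or general linear mixed model (GLMM) may be used depending on the data". It continues by making NDI the dependent variable, with "independent fixed factors time (baseline, 3 months, and 15 months after start of intervention) and group (A and B"). The groups are labelled A and B; the Intervention section's use of group A shows that A is NSE and B is NSEIT. No time-by-group term, baseline covariate or visit contrast is written, and none is ruled out.

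The decision rule is in the same section: "A non-inferiority border of less than 7% was chosen for mean NDI scores", and "the significance level was set to 5% (*p* > 0.05), which corresponds to the one-sided confidence interval (95% CI"). Non-inferiority is concluded when the upper limit lies below the border. The section does not say which model or which contrast supplies that limit.

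**The concern.** The article makes baseline a level of the outcome's time factor and then lists group beside it. A model with those two terms and nothing else has one group coefficient, assumed constant across baseline, 3 and 15 months. Randomization makes the baseline difference zero in expectation, so the coefficient mixes a known zero with the two differences of interest.

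Two things follow. First, the listed terms do not deliver the hypothesis, which asks about each follow-up separately. Second, dilution toward zero is anti-conservative in a non-inferiority trial, because it pulls the upper limit away from the border and toward the conclusion the trial hopes to reach. A loss of effect confined to one follow-up, for instance at 15 months, could be masked by equality at the other two visits.

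**Working it through.** **Inputs from the Statistical analysis section.** SD 13.4; border 7 NDI percentage points; one-sided 5%; 47 per group for 80% power; 70 per group planned.

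**Assumed, not in the article.** Equal SD at all three visits, complete data, and within-person correlation ρ of 0.5-0.7 (0.3 as an extension).

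**Step 1: reproduce the plan's own figure.** For a two-group comparison at one visit with true difference 0, n = 2 × 13.4² × (1.645 + 0.842)² / 7² = 45.3, so 46 by the normal approximation. With the noncentral t, power is 79.997% at 46 and 80.8% at 47. The stated 47 is reproduced. It corresponds to an ordinary two-group comparison and is unaffected by this point.

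**Step 2: what the literal model estimates.** With visit covariance matrix V, the time + group model estimates the group effect as a weighted average of the three visit differences, with weights V⁻¹1 / (1′V⁻¹1). Under compound symmetry (a random intercept) each weight is 1/3, whatever ρ is. True differences NSEIT minus NSE of (0, 7, 7) give

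(0 + 7 + 7) / 3 = 4.67.

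The coefficient reaches 7 only when both follow-up differences are 7 / (2/3) = 10.5.

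**Step 3: chance of declaring non-inferiority at a margin-sized deficit.** SE = √[2 × 13.4² × (1 + 2ρ) / (3n)], and P = Φ((7 − 4.67)/SE − 1.645).

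| n per arm | ρ | SE | P(declare non-inferiority) |
|---|---|---|---|
| 47 | 0.5 | 2.26 | 27% |
| 47 | 0.7 | 2.47 | 24% |
| 70 | 0.5 | 1.85 | 35% |
| 70 | 0.7 | 2.03 | 31% |

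The nominal rate is 5%. At ρ = 0.3 the figures are 31% (n = 47) and 41% (n = 70). If the 95% interval is read as two-sided (nominal 2.5%), the four cells of the table become 18%, 16%, 24% and 21%.

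**Step 4: deficit at one follow-up only.** With a difference of 7 at one follow-up and 0 at the other, the expected coefficient is 7/3 = 2.33. The same formula gives 60-81% over the four cells. Because the weights are equal, it does not matter which follow-up carries the deficit.

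**Step 5: sensitivity to the covariance.** The weights are unequal under an unstructured covariance. With correlations 0.6 (baseline and 3 months), 0.5 (baseline and 15 months) and 0.7 (3 and 15 months) and equal SDs, baseline takes 0.41 of the weight, and the expected coefficient is 7 × (1 − 0.41), or 4.14 unrounded. With a baseline SD of 11 and the same correlations, baseline takes 0.65 and the coefficient is 2.42. Both covariances are illustrations; they show that one third is not an upper bound on the dilution.

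**Step 6: simulation.** In 200 simulated trials (n = 70 per arm, ρ = 0.5, random-intercept fit), the time + group model gave a mean estimate of 4.52 and declared non-inferiority in 37%. With the time-by-group term, the 3-month contrast averaged 7.00 and declared it in 7%. With 200 runs the simulation error is about √(0.35 × 0.65 / 200) = 3.4 percentage points on the first rate and √(0.05 × 0.95 / 200) = 1.5 on the second, so both agree with the formula values of 35% and 5%.

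**The case against.** A reader might infer that the trial has fixed a main-effects-only model and that its primary test is therefore biased. The article does not support that, for four reasons.

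- It lists factors and gives no formula. It does not say that the interaction is left out, and a condensed article may leave interactions and contrasts to the full protocol or analysis plan.
- The mixed model is introduced as something that may be used, and the same section allows other parametric or non-parametric between-group comparisons.
- The confidence interval is never tied to the group coefficient. The sentence after the model returns to non-inferiority, but nearness does not name a contrast.
- The border is set on mean NDI scores, the hypothesis names the two follow-ups, and the 47 per group is the size for a single two-group comparison. All three fit a visit-specific test at least as well as a pooled one.

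These arguments stand, and they remove any claim that the bias is an established property of the trial. They do not remove the mismatch. The article is not silent here: it states terms for the primary outcome and expressly puts baseline among the outcome's time levels. If an interaction is intended, the one term that carries the treatment effect at each follow-up is missing from the list. If it is not intended, the test is anti-conservative. Either way, the listed terms do not produce the comparisons in the hypothesis.

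**Conclusion.** The point holds in conditional form. As written, the only stated NDI model does not yield the 3- and 15-month contrasts that the hypothesis needs. If its group coefficient were compared with the border, the test would lean toward non-inferiority, with a false-positive rate about five to seven times nominal (24-35% against 5%).

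That size rests on four conditions: the mixed model is used, no interaction is fitted, the group coefficient supplies the interval, and the assumptions on covariance and complete data hold. The article commits to none of the first three and gives no correlation. The one-third dilution under compound symmetry does not depend on the correlation; the error rates do.

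This should be fixed; confidence is moderate, because the intended contrast may well be the right one and simply not be written down.

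**What to change.** State the model and the contrast together. Either of these would do:

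- Model NDI at 3 and 15 months with group, time, group-by-time and baseline NDI as a covariate.
- Keep all three visits as outcomes with group-by-time, and constrain the group means to be equal at baseline.

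Then say that the non-inferiority rule applies to the upper confidence limit of the model-estimated NSEIT minus NSE difference at 3 months and at 15 months, and not to a group main effect.

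The cost is one sentence in the Statistical analysis section or the analysis plan. No new data are needed, because baseline measurements must already be completed for inclusion, and the sample size calculation stands. If the full analysis plan already specifies this, a cross-reference is enough.
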